## Abstract

**Background:**

Digital interventions for mental health are pivotal for addressing barriers such as stigma, cost, and accessibility, particularly for underserved populations. While the effectiveness of digital interventions has been established, poor adherence and lack of engagement remain critical factors that undermine efficacy. Millions of individuals will never have access to a trained mental health care practitioner, underscoring the need for highly tailored and engaging self-guided resources. This study builds on a prior study that successfully leveraged behavioral economics (nudges and prompts) to enhance engagement. Expanding on that study, this research will focus on building a foundational dataset of behavioral phenotypes to support artificial intelligence (AI)–driven personalization in digital mental health.

**Objective:**

This 6-arm randomized controlled trial aims to analyze user engagement with randomized tips and to-do lists within a resiliency course tailored for Ukrainian refugees affected by the ongoing humanitarian crisis (Спільна Сила), using the EvolutionHealth.care (V-CC Systems Inc) platform. Insights will inform the development of an AI-based personalization system to optimize engagement and address behavioral health challenges. Secondary objectives include identifying demographic and behavioral predictors of engagement and creating a scalable, culturally sensitive intervention model.

**Methods:**

Participants will be recruited through digital outreach, enrolled anonymously, and randomized into 6 groups to compare combinations of tips, nudges, and to-do lists. Engagement metrics (eg, clicks, completion rates, and session duration) and demographic data (eg, age and gender) will be collected. Statistical analyses will include a comparison between arms and interaction testing to evaluate the effectiveness of each intervention component. Ethical safeguards include institutional review board approval, informed consent, and strict data privacy standards.

**Results:**

This protocol was designed in January 2025. α and β testing of the intervention are scheduled to begin in July 2025, with a soft launch anticipated in August 2025. The experiment will remain active until the sample size requirements are met. Live monitoring and periodic data quality checks will be conducted throughout the study duration.

**Conclusions:**

This trial represents a novel approach to behavioral health research by leveraging randomized experimentation to develop AI-ready behavioral datasets. By targeting an underserved and culturally sensitive population, it contributes critical insights toward scalable, personalized digital mental health interventions. Findings may help inform future digital health efforts that aim to improve engagement, accessibility, and long-term adherence.

**Trial Registration:**

Open Science Framework 34rmg; https://osf.io/34rmg

**International Registered Report Identifier (IRRID):**

PRR1-10.2196/73773

## Introduction

### Background

Self-guided digital mental health interventions play a crucial role in overcoming barriers such as stigma, cost, and accessibility, particularly for underserved populations [1-3]. While their efficacy is well documented in meta-studies [4-7], low adherence and lack of engagement limit their potential impact in publicly available interventions [8-14]. Improving user engagement is therefore essential to realizing the full public health value of these scalable tools.

Optimizing engagement is crucial, as research suggests dose-response relationships; higher engagement is associated with better outcomes such as improvements in mental health [15-17]. This mirrors the commercial world, where higher user engagement results in increased revenue [18,19], and research investigating ways to enhance participation is common.

For example, a 2015 study revealed that LinkedIn (Microsoft Corporation) conducted over 400 controlled engagement experiments per day [20]. The language app Duolingo (Duolingo, Inc) regularly conducts controlled experiments to assess the impact of features to make learning more engaging [21]. Meta (Facebook and Instagram) teaches and technically enables business customers to conduct randomized A-B experiments to optimize ad messaging and conversion [22].

Leveraging similar strategies that commercial platforms use to increase engagement holds the potential to both enhance the user experience in digital mental health and improve overall effectiveness. To that aim, this study builds on prior research on the EvolutionHealth.care (V-CC Systems Inc) platform, which leveraged behavioral economics to tailor user experiences to increase platform engagement [23,24].

For reasons described below, there is a need for further research in optimizing self-guided digital health [25-27], which falls far behind other large-scale commercial platforms that also rely on increasing engagement. Unlike large-scale commercial platforms that rigorously test user experience through ongoing experiments, most digital health platforms lack modern personalization methods. This study aims to address that gap by applying insights from behavioral economics and artificial intelligence (AI) to improve real-world adherence.

### Mental Health Care Professional Deficits

Globally, the World Health Organization (WHO) estimates a deficit of 1.2 million mental health professionals [28]. In the United States, 50.6% of adults with any mental illness received treatment [29], and two-thirds of adults with serious mental health illness received treatment [30].

### The Need to Reframe Digital Health Intervention Reach

Traditional digital health delivery models are primarily reaching the serviceable obtainable market (SOM)—individuals who are insured, tech-savvy, and already engaged with health care systems. This leaves a significant portion of the population unserved, including those without consistent health care access or digital literacy. Addressing this gap requires intentional design for broader accessibility and lower barriers to entry. The total addressable market (TAM) for mental health interventions is far broader, encompassing displaced individuals, the uninsured, and underserved populations around the world (Figure 1).

**Figure 1 figure1:**
[figure not shown]
Estimated total addressable market, serviceable available market, and serviceable obtainable market for mental health and substance use in the United States, Canada, and Europe. B: billion; SAM: serviceable available market; SOM: serviceable obtainable market; TAM: total addressable market.

The persistent engagement problem suggests that the field has not yet found scalable ways to reach or retain this wider audience. By focusing on open-access, low-barrier design, and tailoring through AI-driven nudges, this study represents an attempt to move beyond the SOM and explore pathways for digital health scale, first reaching the serviceable available market (SAM)—those who have digital devices but are not accessing interventions—and eventually the TAM, the full population of individuals worldwide, including those excluded by platform, policy, or economic barriers.

### Issues With Telehealth Access

Intensified by the COVID-19 pandemic [31,32], digital health interventions have become increasingly common. Investment in mental health treatment, mainly telehealth, has seen significant growth [33,34]. The surge in interest reflects the urgent need to address access gaps identified during public health crises. However, while funding has increased, sustainable implementation remains a major challenge.

Despite billions in funding [35-37], the telehealth sector faces significant challenges. These include market saturation, intense competition, profitability, and workforce shortages. In addition, high costs related to patient acquisition and retention, coupled with regulatory demands and a projected shortage of trained professionals [28,38-40], continue to hinder long-term sustainability. These issues are estimated to extend into the next decade and affect access [41], so there is a need to mitigate these issues with alternative resources.

### AI Models: Large Language Models Versus Predictive Analytics

In digital health, AI has primarily focused on large language models (LLMs). Predictive analytics has fallen behind the use of LLMs, as they require large amounts of AI training data. However, predictive models have the potential to enable personalized user journeys and improve long-term engagement, making them a vital area for future development.

#### LLMs

LLMs are advanced AI systems trained on vast amounts of text data to understand and generate human-like language. In digital health, LLMs power chatbots and virtual assistants that provide patient support, answer health-related queries, and assist health care professionals with information retrieval. These models can engage in natural language conversations, making them valuable tools for enhancing patient education.

#### Predictive Analytics

Predictive analytics involves analyzing current and historical health care data (including behavioral phenotypes) to forecast future outcomes. By leveraging statistical models and machine learning algorithms, health care providers can predict disease progression, patient admissions, and treatment responses. This proactive approach can enable personalized care and tailor user experiences, ultimately improving patient outcomes and operational efficiency.

### Russia’s Invasion of Ukraine and Resulting Displacement

In February 2022, Russia initiated a full-scale invasion of Ukraine, leading to widespread destruction and a significant humanitarian crisis. As a result, millions of Ukrainians have been displaced both internally and internationally, seeking refuge in various countries worldwide.

While exact figures are challenging to determine, Los Angeles has a significant Ukrainian community. The city has seen an influx of Ukrainian refugees since the onset of the war, with many individuals and families seeking to rebuild their lives in the area [42]. Before the 2022 invasion, approximately 60,000 Ukrainian immigrants resided in the state. Following the invasion, an estimated 20,000 or more Ukrainians have arrived, bringing the total to around 80,000 [43]. Major cities such as Los Angeles, San Francisco, and Sacramento have been primary destinations for these new arrivals.

Nationally, the Ukrainian diaspora includes more than 1.1 million individuals, encompassing both immigrants and those of Ukrainian ancestry. As of 2019, there were approximately 355,000 Ukrainian immigrants in the United States. In response to the 2022 invasion, the US government announced plans to accept up to 100,000 Ukrainian refugees. By late 2022, approximately 85,000 Ukrainians had used the “Uniting for Ukraine” program, which allows refugees with an American sponsor to remain in the country for 2 years [44]. By December 2022, President Joe Biden announced that the United States had accepted roughly 221,000 Ukrainian refugees through various programs [45].

Globally, the conflict in Ukraine has led to the displacement of approximately 6.8 million refugees, with nearly 4 million people internally displaced within the country as of November 2024 [46]. European nations have accepted the greatest number of refugees, hosting around 6 million Ukrainians, with Germany now hosting the largest number [47]. Canada has also received a significant number of Ukrainian refugees, with major cities such as Toronto, Montreal, and Winnipeg welcoming thousands of newcomers and implementing resettlement programs to support housing, employment, and cultural integration [48,49]. This mass displacement represents the largest population movement in Europe since World War II [50].

### Behavioral Economics

#### Overview

Behavioral economics leverages psychological experimentation to develop theories about human decision-making. The field has identified a range of biases around how people think and feel. In this study, we will examine the engagement of users with nudges and behavioral prompts in an ad libitum, self-guided digital behavior change course.

Digital interventions can be customized using behavioral economics to correspond with the needs and behaviors associated with specific user types. Since interventions become more appealing and relevant to each user’s unique needs and goals, this personalized approach may improve user engagement. Content and engagement techniques can be adjusted to better match specific goals and motivations by using data on user interactions and behavior trends. Through making digital interventions accessible [51] and culturally acceptable, personalization based on behavioral economics techniques can assist in fulfilling the various demands of different types of populations.

This study’s engagement strategy aligns with the COM-B model of behavior, in which capability (C), opportunity (O), and motivation (M) interact to generate behavior (B) [52]. Directive tips enhance capability through actionable guidance, social proof, and present bias tips increase motivation, and checklists and gamification create opportunity by simplifying follow-through.

#### Nudge Theory

Nudge theory, popularized in the 2008 book *Nudge: Improving Decisions About Health, Wealth, and Happiness* [53], leverages indirect, positive suggestions to influence decision-making and behavior through designs or changes in the decision environment. The approach has been applied in various fields, including finance, education, and public health.

There is a lack of quality research analyzing the use of nudges in digital health. A 2019 scoping review examined the use of nudges in both web-based and real-world settings in physical activity interventions [54]. Of the 35 publications reviewed, 8 were web-based studies. The authors concluded that although nudging may be an effective approach to promote physical activity, there are large gaps in research, and further studies that are explicitly based on nudge insights are needed.

A 2020 editorial in *Personalized Medicine* addressed the meaningful adoption of nudges in digital health [55]. The authors acknowledged that using nudges in digital health interventions is rare and advocated for the use of nudges to promote positive behavior change. This reinforces the relevance of our trial, which aims to rigorously evaluate nudge-based strategies in a digital health setting.

Nudges must be culturally sensitive and adaptable to different cultural backgrounds [56]. This ensures that interventions work and are accepted in many kinds of cultural contexts. Addressing ethical issues, including consent, privacy, and potential biases in nudge design, is essential as nudges become more common in digital health. Reliability in digital health platforms can be strengthened by ensuring transparency and user control over the use of nudges, which we will use in this study [57].

#### Behavioral Prompts

Behavioral prompts are cues specifically designed to encourage a specific task [58]. In this study, we will use 2 types of behavioral prompts anchored in nudge theory: daily tips and a to-do checklist (Table 1). These prompts are intended to support self-guided action, reinforcing positive behavior without requiring direct human intervention.

An effective approach for boosting user involvement in digital health interventions may be offered by analyzing combinations of behavioral prompts that users engage with. Through machine learning techniques, the dataset emerging from this study may provide insight into which and what prompts work best with specific demographics and usage patterns [59]. By customizing interventions to meet the unique needs of every user, this integrated approach might increase the possibility of long-term behavior change and better health outcomes.

**Table 1 table1:** Example nudges and prompts.

Delivery format	Content type	Example from our study
Tip	Directive content	Express yourself by uploading your image!
Tip	Social proof	Many members have similar goals to yours. Reviewing other members’ goals can help you reach your goal.
Tip	Present bias	Feel better sooner by learning from others. Read what others have posted in the community.
Prompt	To-do checklist	Watch the getting started video.
Visual element	Gamification	A progress bar fills as users complete sections of the course.

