### Randomization

Participants will be randomly assigned to one of the following six arms, as presented in Figure 2:

Arm 1 (baseline control): directive tips only and no to-do checklist.Arm 2: directive tips + social proof tips and no to-do checklist.Arm 3: directive tips + social proof tips + present bias tips and no to-do checklist.Arm 4: directive tips + to-do checklist.Arm 5: directive tips + social proof tips + to-do checklist.Arm 6: gamification (progress bars) + to-do checklist.

Participants will be randomly assigned to one of the six experimental arms using computer-generated randomization in a 1:1:1:1:1:1 ratio. Randomization will be conducted at the point of user registration, ensuring equal probability of assignment to any condition. No stratification or blocking will be used, as randomization is expected to produce comparable groups given the planned sample size. Randomization will be logged automatically by the system to ensure reproducibility and allocation integrity.

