### Multiarm Trial Rationale

The six study arms were developed to explore the individual and combined effects of behavioral prompts grounded in behavioral economics, to identify which strategies most effectively enhance engagement in a digital resiliency program. Each arm includes a specific configuration of tips, checklists, or gamification elements intended to test distinct motivational mechanisms. This design enables comparative analysis across different engagement strategies while remaining operationally feasible. These components tested include (1) directive tips, grounded in the theory of implementation intentions, which provide straightforward, actionable guidance; (2) social proof tips, which leverage peer effects by referencing the behavior of others to encourage participation; (3) present bias tips, designed to counteract temporal discounting by emphasizing short-term benefits of engagement; (4) to-do checklists, which introduce structured goals and progress-tracking to increase adherence; and (5) gamification, which builds intrinsic motivation through visual indicators of advancement and progress feedback.

While a full factorial design could have explored all possible combinations of these interventions, the current 6-arm structure is a deliberate balance between conceptual rigor and practical feasibility. This structure enables comparative analysis across a diverse set of nudge combinations without creating an unmanageable number of trial arms. It was also informed by operational constraints and the need for meaningful data distribution across arms.

Our study design is also a foundational step toward developing a predictive analytics dataset. The behavioral engagement data collected through the six arms will be used to build baseline models that inform AI-driven personalization strategies. Future iterations of the course will be updated with tailored nudges based on user profiles, and new user data will be used to validate and refine the models. We chose the current design to generate sufficient diversity and volume in behavioral data to create a baseline for our long-term, adaptive research agenda.

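### To the extent that present bias tips are worded like the Table 1 example, their click rate mixes present bias with social proof and cannot be read as the effect of present bias alone

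*Protocol article*

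**What the plan says.** Table 1 in the Behavioral Prompts section is captioned "Example nudges and prompts" and gives one example per content type, under a column heading that presents them as coming from this study. The three tips are:

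- directive: "Express yourself by uploading your image"
- social proof: "Many members have similar goals to yours. Reviewing other members’ goals can help you reach your goal"
- present bias: "Feel better sooner by learning from others. Read what others have posted in the community"

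The Multiarm Trial Rationale section describes "social proof tips, which leverage peer effects by referencing the behavior of others to encourage participation" and "present bias tips, designed to counteract temporal discounting by emphasizing short-term benefits of engagement". It says that the configuration of each arm is "intended to test distinct motivational mechanisms".

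Under Randomization, present bias tips occur only in arm 3, which adds them to the content of the arm before it ("Arm 2: directive tips + social proof tips and no to-do checklist"). Under Primary and Secondary Outcomes, the primary outcome is a click on an individual tip, a type of tip or a checklist item, and it is the basis for judging which types of prompt start action. Future Directions adds that the data will train models to match prompts to user profiles.

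**The concern.** The definitions separate the two tip types by their active ingredient: reference to other people for social proof, an early benefit for present bias. The present bias example contains both ingredients, so by the plan's own definition it could equally be filed under social proof.

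Random display of tips and a larger sample do not help, because the mixing is inside the text of the tip. Nor does another arm help: no arm shows present bias tips without social proof tips. If many present bias tips are worded like the example, a high click rate for that type could come from the peer cue, from the promise of an early benefit, or from both. The type label carried into the personalization dataset would then describe only part of what the user saw.

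**Working it through.** No stated figure in the protocol depends on this point, so there is none to reproduce. The check has two parts: a comparison of wording, and a simple exposure calculation under stated assumptions.

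**1. Wording against the definitions**

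| Table 1 tip | Early benefit | Reference to others | Course component it points to |
|---|---|---|---|
| Directive | no | no | avatar upload |
| Social proof | no (a benefit, but no timing) | yes | goals exercise |
| Present bias | yes | yes, in both sentences | community |

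The present bias example meets both definitions. The three examples also point to three different components, so a comparison of these tips by type is a comparison by destination as well.

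**2. Type-level click rates**

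Assumptions, none of which is in the protocol: cue effects on the click probability are additive; directive tips carry neither cue; every social proof tip carries the peer cue (effect s) and no immediacy cue; every present bias tip carries the immediacy cue (effect p); a share q of present bias tips also carries the peer cue.

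- Present bias minus directive = p + qs, against p if the tips were clean.
- Present bias minus social proof = (p + qs) − s = p − (1 − q)s. This is p − s at q = 0 and p at q = 1, so what the comparison means changes with q.

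**3. Arm 3 minus arm 2, per displayed tip**

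Further assumption: tip types are displayed in equal shares within an arm.

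- Share of tips with the peer cue: 1/2 in arm 2; (1 + q)/3 in arm 3.
- Share with the immediacy cue: 0 in arm 2; 1/3 in arm 3.
- Difference = p/3 + s[(1 + q)/3 − 1/2] = p/3 + s(2q − 1)/6.

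**4. Numbers with p = 0 and s assumed at 2 to 5 percentage points**

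| q | Peer-cue share, arm 3 | Present bias minus directive, qs | Arm 3 minus arm 2, s(2q − 1)/6 |
|---|---|---|---|
| 0 | 0.33 | 0 | −0.33 to −0.83 points |
| 0.5 | 0.50 | 1.0 to 2.5 points | 0 |
| 1 | 0.67 | 2 to 5 points | +0.33 to +0.83 points |

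For scale only: Our Prior Work reports that members of the earlier trial's two tip arms clicked on 5% of tips. That figure covers all tips and is not broken down by type.

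The type-level distortion rises steadily with q and is zero for clean tips. The arm-level term behaves differently: it has the same size at q = 0 and q = 1, with opposite signs, and vanishes at q = 0.5. It arises because adding a third tip type changes how often the social cue is shown.

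**The case against.** Table 1 is illustrative. It shows one tip per type, the rest of the bank is not in the article, and an article need not print it. The section on cultural adaptation says that tips are still being translated and revised, so the wording may not be final. This stands. A reader might infer that no click on any present bias tip can be credited to present bias; the document does not support that, because q is unknown and the example does contain a genuine immediacy cue.

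A reader might also infer that the overlap spoils the arm 3 against arm 2 contrast and that cleaner wording would repair it. The algebra does not support this. Rewording from q = 1 to q = 0 only turns +s/6 into −s/6, and both arms contain social proof by design.

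It can be argued that the second sentence of the example merely names its destination, the moderated community, and that the social proof example differs by making a claim about what many members share. This has some force. But the first sentence makes other people the route to the benefit, and the plan's definition asks only for reference to others' behavior.

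Finally, Data Collection provides for logging of each tip displayed and clicked, so tips can be recoded later, and the Hypothesis section rests no expectation on present bias. Both points limit the harm. Recoding is weaker than rewording, however: if every present bias tip carried the peer cue, no tip would show immediacy alone, and p could be recovered only by assuming additivity.

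**Conclusion.** The point holds for the type-level reading of the primary outcome, in proportion to the share of present bias tips worded like the example. Present bias against directive clicks then estimate p + qs. With no true present bias effect, that is an apparent effect of 1.0 to 2.5 points at q = 0.5 and 2 to 5 points at q = 1, for an assumed s of 2 to 5 points. The sizes rest on additivity and on values of q and s that the protocol does not give; the overlap in the example itself rests on no assumption beyond the plan's definitions.

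The arm 3 against arm 2 contrast should be read as the effect of adding present bias tips to the mix, not as present bias alone. With equal display shares it includes s(2q − 1)/6, which can have either sign and is not caused by the overlap alone. This is a matter of clean measurement and labelling, worth settling before launch; it does not undermine the randomized comparison of the arms as packages.

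**What to change.** 1. While the adaptation is under way, reword the Table 1 present bias example and any similar tips so that each tip carries one frame.
2. Code every tip for all the cues it carries (immediacy, peer, directive) and for the course component it points to.
3. Analyse type-level clicks by those cue codes, with the target component in the model. Leave tips that cannot be separated out of the single-type comparison.
4. State that arm 3 against arm 2 estimates the effect of adding present bias tips to directive and social proof tips.

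The cost is text editing and a coding sheet; arms, sample size and schedule are unaffected. The downside is that some tips will be rewritten or excluded. Present bias tips that promote the community are also harder to write without mentioning other members, so removing the peer reference may tie tip type more closely to destination. That is why the target component belongs in the type-level model.
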